### Step 2: Integration of a new working environment tool – the dialogue

The first component in the second step is the implementation of a structured dialogue between the supervisor and each employee at 3-week intervals about work environment challenges and health. The possible topics of the dialogues are broad to ensure that a relevant dialogue can be held for all employees, with or without pain. On the basis of the joint knowledge in the organization obtained through the courses and the resource assessment in the formative evaluation, the objective of the dialogue is to optimize prevention and handling of health challenges related to work. The dialogue has three primary aims: 1) to generate a space where the employees feel comfortable to discuss work and health-related challenges, 2) to provide the supervisor with tools for facilitating a constructive dialogue focused on identifying possible solutions; and 3) Identify current work or health challenges for each employee and use knowledge from the courses to generate a plan for specific, realistic and effective actions. The plans can involve everything from participatory ergonomics (e.g. lifting equipment or changes in the organization of the work) to health-promoting initiatives such as physical or cognitive training or a combination of these.

The supervisors are responsible for scheduling the dialogue approximately every 3rd week. A tablet-based dialogue-guide is developed and all supervisors and management receive a tablet-pc for this activity. A log-on system ensures that only information about the specific employee is available on the tablet during the dialogue. The dialogue guide is tablet-based to encourage moving the dialogue out of the manager’s office.

The first time an employee is logged in, the employee is asked to answer 2 questions; 1) How much has pain affected your work during the last three weeks? (on a scale from 0 to 10) and 2) Which elements in your work do you find most challenging? (open-ended). If the employee identifies challenges at work, the employee and supervisor together develop a plan for overcoming the challenges and preventing or reducing pain and consequences of pain. The plan is registered in the dialogue guide at the tablet. The following meetings will begin with a question about to what degree the plan has been fulfilled (on a scale from 0 to 10).

The registrations are uploaded to a web-interface, available to the researchers. If the dialogue is not held the omission will be registered, making it possible for the researchers to contact the local coordinators at the specific workplace and determine how the implementation of the dialogue can be further supported prospectively.

### Sustainability initiatives to support the process

Throughout the intervention period (1 to 2 years, depending on when the nursing home steps into the intervention) initiatives will be made to motivate and engage participants. First, the concepts of the project are participatory to ensure that the intervention is tailored to the specific needs of the participants (expecting that needs change over time), facilitating ownership and motivation to sustain the initiatives. Regular meetings of the entire organization will ensure that all are informed about the main features, purposes and processes of the project. The researchers will encourage health and work environment issues to be on the agenda in multiple settings (e.g. at staff meetings, in the team coordination) and continually facilitate initiatives to remind the supervisors and employees about the key messages. This will for example be done through special events at the workplace and organizing theme weeks using posters and roll-ups at the workplace. Furthermore there is a booster session, a course of 3 h approximately every half year for both management and employees. These courses both have the purpose of following-up on the topics from the last course, to handle challenges currently at the workplace, and to prepare new employees to engage in the dialogue.

The intervention is delivered by research staff but the workplaces will be encouraged to continue both the courses and the dialogue after the intervention period.

## Study design

The study is described in accordance to the guidelines of the Trend Statement [41]. In clinical intervention research, the randomized controlled trial is considered the gold standard. However, in workplace settings this can be practically and logistically impossible and can hamper implementation due to logistical issues and impaired organizational commitment [42, 43]. Moreover, it is not possible to implement the intervention in several clusters simultaneously within the resources of the study, because of the amount of practical and logistical resources needed to implement the intervention in each workplace.

These difficulties can be handled by using the more feasible, quasi-experimental stepped wedge design [42, 43], with gradual implementation of the intervention in the workplaces. A stepped-wedge design is a type of one-way crossover study in which clusters cross over from the control arm to the intervention arm at different time points (Fig. 3). Enrollment in the study will be determined between the management and the researchers. This process of enrollment will permit the researchers to focus study resources on the initial phase at one workplace at a time, to ensure that each workplace is prepared and motivated to start.

**Fig. 3 Fig3:**
[figure not shown]
The quasi-experimental stepped-wedge intervention design, allows for repeated measures at each workplace before and after the intervention-period

Repeated measurements will be conducted in each workplace throughout the intervention period. Baseline measures will start at the same time for all clusters, making it possible to have repetitive baseline measurements for the clusters not enrolling in the study initially.

The project has been approved by the Danish Protection Agency and is reported to the ethical committee. The local ethics committee has evaluated a description of the study and concluded that, according to Danish law as defined in Committee Act § 2, 1, an organizational intervention evaluated merely by questionnaires should not be further reported to the local ethics committee (Protocol H-1-2013 FSP). Following the committee § 1 paragraph 5 declaration of the project is therefore not relevant and the project can be implemented without further approval from the ethics committees of the Capital Region. The collection of questionnaire follows the requirements of the Helsinki declaration.

### Effect and process evaluation

A program logic model is made to illustrate all steps in the intervention and their evaluation (Fig. 4). The effect of the intervention will be measured on the primary outcome of Pain intensity (unspecified MSD) and the secondary outcomes of Bothersomeness, sickness absence, individual health literacy, organizational health literacy and fear avoidance.

**Fig. 4 Fig4:**
[figure not shown]
The program logic model of the study illustrates the 2 steps of the intervention and the components within these steps for both employees and management and the concurrent steps of the evaluation

#### Data collection

The data collection consists of both quantitative and qualitative measures, obtained from questionnaires collected though text messages, logbooks from instructors in the intervention, data from dialogue guide and qualitative interviews and logbooks about maintenance initiatives at each workplace.

Quantitative data will be collected through text messages delivered by the SMS Track® system [44]. The setup of the software is designed for the study in close cooperation with researchers. Every 4 weeks (on a Monday) the respondents receive an automated text message to their private mobile phone, which they are expected to answer by text message. Baseline measurements as well as repetitive measures before and after the intervention are made at all workplaces. The respondents will receive 4 questions every 4 weeks on pain intensity, bothersomeness, pain-related sickness absence and one item on organizational health literacy (providing information about possibilities for prevention and handling of pain). Every 12 weeks the respondents will receive additional 9 questions on individual and organizational health literacy and fear avoidance [45].

Before baseline, all employees will be thoroughly informed that the data collection is about to start, that it is a scientific data collection and that it is anonymous and voluntary and that they can withdraw from the data collection at any time, with no questions asked. At baseline, text message questionnaires are sent to all employees. Employees not responding to the text message will be reminded after two days with a text message reminder and if there is still no response the employee will be called by telephone to check if the phone number is correct and, if it is, whether the employee has chosen not to participate in the scientific evaluation.

Qualitative data will be collected through interviews with the municipality director of health and care, the managers at the nursing homes, focus groups with all supervisors at the workplaces and representatives from employees and employee union and work environment representatives (6-8 pers.). The interviews will be conducted before baseline and after six months. Semi-structured interview guides will be used to secure that the interviews will uncover the existing framework for supporting employees with health and work environment challenges and possible barriers and facilitators for implementation. The interview guide will make room for the respondents to contribute with thoughts relevant for the implementation and normalization of the intervention [46]. These qualitative data will be analyzed using NVivo and based on the four elements in Normalization Process Theory (NPT) (see below).

To register the participation, engagement and delivery of the courses, all instructors will complete a logbook after each course. Data from the dialogues will be available to the researchers through a web interface where all questionnaires from completed dialogues are accessible. Other logbook entries will describe all maintenance initiatives at each workplace.

#### Pain, bothersomeness and sickness absence

Because pain is often a fluctuating condition, which can be difficult to recall [47], monthly monitoring of pain, bothersomeness and pain-related sickness absence will be conducted. Pain is measured as highest intensity of pain in the muscle and joints every 4^th^ week by the text messages [48]. The respondents will be asked to answer on a 10-point scale with 0 being no pain and 10 being worst imaginable pain. The question posed is “During the previous four weeks, on a scale from 0 – 10, what was the highest intensity of pain in your muscles and joints? (0 = no pain, 10 = worst imaginable pain) [49] Pain-related sickness absence will be measured by posing the question: How many days within the past 4 weeks, have you been absent from work because of pain in muscles and joints? (Answer with a number from 0 to 28) [50].

Bothersomeness will be measured by posing the question: “How many days during the previous 4 weeks have pain in muscle and joints affected your work routines? (Answer with a number from 0 to 28) [49] In addition company-registered sick-leave will be abstracted from the management information system database.

#### Individual and organizational health literacy

Individual health literacy is operationalized as knowledge about prevention and handling pain, competences to understand, interpret and use information to improve own health and the work environment. This will be evaluated using a questionnaire validated for the specific purpose of this intervention, with items inspired by among others the Health Literacy Questionnaire (HLQ) [51], which has recently been translated into Danish. A validation of our specific questionnaire was conducted using psychometric analysis, test-retest measurements using text messages and cognitive interviews with nurses’ aides. One workplace health literacy item will be monitored monthly and the remaining items will be monitored every 12 weeks.

Organizational health literacy is defined as providing/communicating understandable information, facilitating prevention and supporting handling of health challenges. To capture health literacy at the organizational level, each employee will evaluate their supervisors’ role as a provider of understandable information, facilitator of pain prevention and supporter of handling and acting upon health challenges. Additional qualitative measures will be obtained through the process evaluation (below).

For assessment of organizational health literacy, one question covers the degree to which the supervisor helps the employee to identify options to prevent and manage pain in the workplace: How much do you agree in the following: Your supervisor helps you to identify which possibilities you have to prevent and manage pain? To capture the supervisors’ function as a health information provider, two questions will be posed: 1) How much do you agree in the following statement: Your supervisor does something active when you inform him/her about your pain? and 2) How much do you agree in the following statement: It is easy to find solutions at the workplace, if you experience pain in your body?. Three questions assess the quality of the communication between employee and supervisor: 1) How much do you agree in the following statement: When I feel pain and discomfort in the body, my supervisor really understands what I’m going through? and 2) How much do you agree in the following statement: It is easy to have good discussions about pain and discomfort with your supervisor? and 3) How much do you agree in the following statement: It is easy to get to talk to your supervisor?.

To capture the individual health literacy the following questions are posed: How much do you agree in the following statement: There are things I do regularly to prevent pain and discomfort in the body? and How much do you agree in the following statement: I am sure I have all the information I need to handle pain and discomfort in the body, the best possible way ?.

#### Fear avoidance

The effect on fear avoidance will be evaluated by one item [45]: Here is a statement about pain that others with pain problems have told us about. To what extent do you agree with the statement: I should not perform my normal activities or my normal work routines with my current level of pain (Answer with a number between 0 (completely disagree) to 10 (strongly agree)). Based on the validation of the questionnaire we decided to include this question knowing that other factors than fear avoidance can affect the answer to this question.

#### Process evaluation

The process evaluation will identify the level of implementation and the barriers and facilitators for complete implementation (i.e. normalization). Normalization process theory will be used to evaluate the process and each step in the intervention. Normalization process theory (NPT) is a framework for developing, evaluating and implementing complex interventions [34]. Through the use of NPT it is possible to identify factors that promote or inhibit the routine incorporation of complex interventions into everyday practice, i.e. normalization [52]. In addition a participatory component is recommended in needs assessments, to evaluate the workplace readiness for change and to optimize the tailoring of the intervention to the specific needs and resources at each workplace [34, 37, 38]. NPT focuses on the work that individuals and groups do to enable an intervention to become normalized.

There are four main components to NPT: coherence (or sense-making); cognitive participation (or engagement); collective action (work done to enable the intervention to happen); and reflexive monitoring (formal and informal appraisal of the benefits and costs of the intervention) [34]. These components are dynamically interconnected and interact with the wider context of the intervention, such as organizational context, structures, social norms, group processes and conventions.

In this study NPT will be used to evaluate the workplace readiness for organizational health literacy (i.e. does the intervention make sense to the employees, are they motivated to participate, how does the intervention fit into the existing structures in the organization). Likewise the tailoring of the intervention to the specific needs and resources at each workplace will be based on the workplace evaluation using NPT. Furthermore we will use the NPT in the evaluation of the process of implementing each of the elements in the intervention, to better understand the evaluation of the effect of the intervention. In the preparation phase, we will uncover the workplace readiness for organizational health literacy through interviews with employees, supervisors, management and the director of health and care in the municipality. The interviews will uncover the existing framework at the workplace for supporting employees with health and work environment challenges. Furthermore the local barriers for implementing organizational health literacy will be identified as well as existing organizational structures which can support the implementation (e.g. health promotion initiatives at the workplace, workplace meetings, organization of working environment representatives).

Approximately 6 months after the initiation of the courses, we will evaluate the process of implementing the intervention qualitatively through interviews with all levels of the organization. Here the challenges and positive factors in each of the four phases; the preparation phase, the courses, the dialogue and the maintenance phase will be uncovered retrospectively. Here the organizational health literacy will also be evaluated qualitatively. Furthermore, the employees, supervisors and managers experiences with pain, bothersomeness and sickness-absence will be uncovered.

### Courses

During the courses we will measure how many employees participate in each course. The instructors will register the execution of each course in a logbook including whether or not content was delivered according to the intervention protocol, degree of participants’ engagement, etc.

### The dialogue

We will measure the registration of completed dialogues through the web interface where the questionnaires are accessible. Furthermore we will measure the number of plans registered by employees and supervisors and to what degree the plans have been executed. The implementation of the dialogue between the employee and the manager will be evaluated qualitatively using focus group interviews with representatives from the employees and interviews with supervisors and managers. The level of concordance between the action generated by the employees and the supervisors will be compared [53].

### Maintenance initiatives

During the intervention period we will keep a log book on the initiatives at the workplace related to building or supporting organizational health literacy, such as meetings with specific health-related topics on the agenda, posters, roll ups, and health-related “theme days.”

### Sample size calculation

For sample size calculation we used the method described by Hussey et al. 2006, for the stepped wedge design [54]. The sample size is calculated for pain intensity (numeric rating scale 0-10). Pain intensity variance was set to be 2.1 based on a study by Kovacs et al. on patients with non-specific low back pain. We estimated a potential effect size of 0.5 after 6 months’ intervention. With an α of 0.05, a power of 0.8, and an intracluster correlation coefficient of 0.05, we calculated that we needed 130 participants in a stepped-wedge trial to allow analyses of effect on pain intensity. Due to a general level of 20 % in employee turnover and risk of drop-out from questionnaire survey from other reasons, we added another 20 % to the sample size. Thus a minimum of 150 individuals have to be included in the stepped-wedge-designed evaluation.

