## Background

Musculoskeletal disorders (pain) are a considerable societal problem because of the prevalence, the pervasive impact on the individual, and the scope of the individual and socio-economic consequences. The consequences include reduced quality of life for the individual, increased sickness absence at the workplace, and economic consequences for the society [1–3]. Within short educated job groups there is a high prevalence of pain, especially within job groups with high physically demanding work [4]. For example, the annual prevalence of low back pain among nursing aides is reported to be more than 60 % in Denmark [5]. Pain may lead to functional impairments, and the combination with physically demanding work tasks, such as patient handling in health care institutions and home care, substantially increase the risk of consequences of pain such as impaired quality of life, work disability, sickness absence and early exit from the labor market [2, 3, 6–8].

During the past decade, management in Danish nursing homes and home care has initiated a number of initiatives to improve the working environment, such as “no lift programs” or programs to increase employee involvement in decision-making and in health and safety issues [9]. Despite these efforts, the workers still report heavy lifting, high physical and emotional work demands, and an inadequate decision-latitude (high degrees of responsibility concomitant with low decision-latitude) [10, 11]. Thus, there is not a clear connection between the work environment efforts reported from management and experiences of employees. Discrepancies between effort and effect of workplace health initiatives is a well-known issue, with implementation challenges reported by several in the past decade [12, 13]. Problems with compliance and participation are recognized challenges in studies with low-educated workers in workplace settings [14–17], increasing the risk of low effectiveness [18, 19] in groups with the most severe occupational exposures and health needs.

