### Participants/study population

The participants in the study will be employees in elderly care in nursing homes in one municipality. The main employees in the elderly care in the municipality are nurses’ aides who are either trained social - and health service (SHS) aides or helpers. The managers are primarily nurses. In Denmark, SHS helpers have 14 months of training, SHS aides have an additional 6 months of training. All employees working in the nursing homes are eligible to participate in the study. It is a workplace decision to participate in the intervention which is conducted fully during work hours. All permanent staff at each workplace - including the kitchen, cleaning and technical staff – will be part of the intervention. Thus, the study population consists of short-educated service- and blue-collar workers in elderly care, but will be referred to as nurses’ aides because the majority of the employees belong to this profession. Whether temporary staffs are such an embedded part of the organization that they should participate in the intervention will be decided by the manager at each workplace. Supervisors and top management will also participate in the intervention.

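### The planning variance of 2.1 comes from low-back-pain patients, not from all nursing-home staff, so the stated 80 % power at 130 participants is unsupported

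*Protocol article*

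**What the plan says.** In the protocol article, under Sample size calculation, the planning inputs are for pain intensity on a 0–10 numeric scale. The article states "Pain intensity variance was set to be 2.1 based on a study", and describes that study as one "on patients with non-specific low back pain". The target is given as "We estimated a potential effect size of 0.5 after 6 months". The calculation continues "With an α of 0.05, a power of 0.8, and an intracluster correlation coefficient of 0.05", and the result is "we calculated that we needed 130 participants in a stepped-wedge trial".

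The population is set out under Participants/study population: "All employees working in the nursing homes are eligible to participate in the study". Kitchen, cleaning and technical staff are part of the intervention, and there is no pain criterion. The section on the dialogue (Step 2) confirms that pain-free staff belong to the target group; its topics are kept broad "to ensure that a relevant dialogue can be held for all employees, with or without pain". The section on pain, bothersomeness and sickness absence defines the primary outcome as the highest pain in muscles and joints over the previous four weeks, with 0 for no pain. The Statistical analysis section plans a multilevel model that allows for clustering and for repeated measurements on the same person.

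**The concern.** The variance and the outcome belong to different populations. A variance of 2.1 (SD 1.45) describes people selected because they have pain, at one body site. The trial analyses a mixture of people at 0 and people with pain somewhere, on a worst-pain item. Such a mixture usually has a larger variance than its painful part. The article gives no reason for carrying 2.1 over, no variance for all staff, and no sensitivity range. The only prevalence it offers is in the Background: "the annual prevalence of low back pain among nursing aides is reported to be more than 60" per cent. That figure is annual, for the low back only, and for nursing aides only.

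At a fixed design and intracluster correlation, the required sample size is nearly proportional to the variance. If the true variance is about twice 2.1, the statement that 130 people give 80 % power does not hold on the method it cites, and a null result could be read as stronger evidence of no effect than it is.

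**Working it through.** **Inputs.**
- From the article: variance 2.1, effect 0.5, α 0.05, power 0.80, intracluster correlation (ICC) 0.05, N = 130.
- Assumed, because the readable text does not give them: two-sided test; 0.5 in scale points; one home crossing per step; one measurement per step; number of homes I, with I + 1 periods; share with pain p; mean worst pain m among them; variance 2.1 within that group.

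**1. Reproduce 130.** The Hussey-Hughes variance of the effect is

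Var = I·s²(s² + T·τ²) / [(I·U − W)s² + (U² + I·T·U − T·W − I·V)τ²]

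where s² is the residual variance divided by the number per home and τ² is the between-home variance. U is the number of treated home-periods. W and V are the sums of squared column and row totals.

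For I = 5, T = 6 and 26 per home: U = 15, W = V = 55, τ² = 0.05 × 2.1 = 0.105, s² = 1.995/26 = 0.0767.
- Numerator: 5 × 0.0767 × (0.0767 + 0.630) = 0.271
- Denominator: 20 × 0.0767 + 70 × 0.105 = 8.88
- Var = 0.0305, SE = 0.175
- Power = Φ(0.5/0.175 − 1.96) = 0.82

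The N needed for 80 % power is 218, 158, 125, 103, 75 and 59 for 3, 4, 5, 6, 8 and 10 homes. If 2.1 is read as the within-home variance, five homes need 132 and power at 130 is 0.80. Of the layouts tried, only five homes comes close to 130, so five is used below. It remains an assumption.

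**2. Variance in all staff.** If pain-free staff score 0, the total variance is p × 2.1 + p(1 − p)m².
- p = 0.8, m = 4: 1.68 + 2.56 = 4.24
- p = 0.6, m = 4: 1.26 + 3.84 = 5.10
- p = 0.6, m = 2: 1.26 + 0.96 = 2.22

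This exceeds 2.1 only when m > √(2.1/p), that is, above 1.87 at p = 0.6, 1.62 at p = 0.8 and 1.53 at p = 0.9.

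**3. Power at 130 by the stated method** (five homes, no within-person correlation). At fixed ICC, the SE scales with the square root of the variance.
- Variance 2.22: power 0.80, N needed 132
- Variance 4.24: SE = 0.175 × √(4.24/2.1) = 0.248, power 0.52, N needed 261
- Variance 5.10: SE = 0.272, power 0.45, N needed 316

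**4. Allow for the same people being measured repeatedly.** Let a share r of the total variance be a stable person effect. Then s² becomes (0.95 − r) × variance/26, and τ² is replaced by τ² + r × variance/26. For variance 4.24 and r = 0.5: s² = 1.908/26 = 0.0734, and τ² becomes 0.212 + 0.0815 = 0.2935. This gives Var = 0.673/22.0 = 0.0306, SE 0.175 and power 0.82.

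| Person share r | Power, variance 4.24 | Power, variance 5.10 |
|---|---|---|
| 0 | 0.52 | 0.45 |
| 0.3 | 0.67 | 0.59 |
| 0.5 | 0.82 | 0.74 |
| 0.6 | 0.90 | 0.84 |

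**The case against.** **The planned analysis uses repeated measures.** This is the strongest reply. The variance that the mixture adds is the gap between pain-free and painful staff. If pain status were fully stable, that gap would be entirely between persons: 2.56/4.24 = 60 % or 3.84/5.10 = 75 % of the total. At such shares, power at 130 exceeds 0.80. Two or three four-weekly measurements per step would also help: at variance 4.24, power is 0.80 or 0.93 even without a person effect, though this treats residuals as independent and is optimistic. Most of this stands. It is limited by the article's own description of pain as fluctuating, which lowers the stable share. The sample size section also states no within-person correlation, so the 80 % cannot be credited with this gain.

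**The inputs p, m and five homes are assumed.** This is true. With a mean near 2 the loss is negligible, and below about 1.5–1.9 the direction reverses. Nothing in the article suggests so low a mean on a four-week worst-pain item, but nothing excludes it.

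**The 0.5 has no stated unit.** If it is standardised, the variance drops out of the calculation, and a plain two-arm comparison would need 126–128 in total, also close to 130. A stated variance, a named 0–10 scale and a cited stepped-wedge method point to scale points, but the text does not settle it.

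**Stronger readings that the article does not support.** A reader might infer that power at 130 is overstated outright. That is not shown for the mixed model that will be fitted. A reader might also infer that the whole average effect must come from staff with pain, because a score of 0 cannot fall. The courses and the dialogue aim at prevention as well, and someone at 0 in one four-week window may score higher in a later one. Preventing that contributes to the effect.

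**Conclusion.** The concern holds as a mismatch between the planning input and the trial population. The variance of 2.1 comes from low-back-pain patients and is applied, without justification, to worst pain at any site in all staff. It is probably too small. By the cited method, power at 130 would be about 0.45–0.52 if 60–80 % of staff report pain with a mean of 4. That range rests on five homes, one measurement per step, a 0.5-point effect and no within-person correlation. With half to 60 % of the variance between persons, it rises to about 0.74–0.90. The 80 % claim is therefore unsupported; the article does not allow a single corrected figure. The point deserves correction because a null result would be read against this power statement.

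**What to change.** Replace 2.1 with the total variance, ICC and within-person correlation estimated from the trial's own text-message pain scores in all employees. Use only scores from before each home crosses over, so that no information on the effect enters. The Study design section plans a common baseline start and repeated baseline measures for homes that cross later, which should supply the data; whether they are already in hand is not stated. Beside the calculation, give the number of clusters and steps (the design figure could not be seen here) and say that 0.5 is in scale points, if that is what was meant. Then restate the power, or the smallest detectable difference, for the number enrolled over a range of these values.

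The cost is one recalculation. Recruitment, outcome and analysis model do not change. The stated power may become less favourable.

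### The minimum of 150 does not follow from 130 participants plus 20 %: that sum is 156, and keeping 130 after a 20 % loss takes 163

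*Protocol article*

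**What the plan says.** The section Sample size calculation in the protocol article builds the recruitment minimum in three linked steps.

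- **Base number.** Under the stated error rate, power and correlation ("With an α of 0.05, a power of 0.8, and an intracluster correlation coefficient of 0.05"), the authors report: "we calculated that we needed 130 participants in a stepped-wedge trial to allow analyses of effect on pain intensity".
- **Allowance.** They then give the reason for enlarging it: "Due to a general level of 20 % in employee turnover and risk of drop-out from questionnaire survey from other reasons". The amount added is 20 %.
- **Result.** The next sentence draws the conclusion: "Thus a minimum of 150 individuals have to be included in the stepped-wedge-designed evaluation".

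The last sentence presents 150 as the outcome of the first two steps. No other section of the article gives a different base number, allowance or minimum that would reconcile them.

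**The concern.** The three figures cannot all be right: 150 is not what 130 and 20 % produce under either usual reading of adding 20 %. The figure matters because it is the recruitment floor for the primary outcome, pain intensity. The trial could enrol exactly 150 people, lose exactly the 20 % it expects to lose, and end with fewer people than its own calculation asks for. A reader also cannot tell which of the three numbers is in error, so cannot tell what level of loss the trial was really sized to withstand.

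**Working it through.** **Inputs, all from Sample size calculation**

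- Number needed before loss: 130
- Power at that number: 0.80; α = 0.05 (sidedness is not stated; two-sided assumed here)
- Allowance: 20 %
- Stated minimum: 150

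The 130 is taken as given. The numbers of clusters and steps are not stated beside the calculation and the design figure is not shown, so it cannot be rebuilt uniquely from the article. The check concerns only the step from 130 to 150.

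**1. Trying to reproduce 150**

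- Adding 20 %: 130 × 1.20 = 156, which is 6 more than stated.
- Retaining 130 after 20 % loss: 130 / (1 − 0.20) = 162.5, rounded up to 163, which is 13 more than stated.

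Neither gives 150. Rounding does not explain it either: 156 to the nearest ten is 160.

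**2. What would give 150**

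- 125 × 1.20 = 150, or 120 / 0.80 = 150. Both need a base other than 130.
- 130 × 1.15 = 149.5. This needs an allowance other than 20 %.

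**3. What 150 actually allows for**

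- Addition: 150 / 130 − 1 = 0.154, or 15.4 %.
- Largest loss that still leaves 130: 1 − 130/150 = 0.133, or 13.3 %.
- Left after a 20 % loss: 150 × 0.80 = 120, which is 10 short of 130.

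**4. Effect on power, on the plan's premise that 130 gives 0.80**

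With the normal approximation, the signal scales with the square root of the number analysed:

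- power(n) = Φ[(1.960 + 0.842) × √(n/130) − 1.960]
- n = 130: Φ(0.842) = 0.80, as it must be
- n = 120: 2.802 × 0.961 − 1.960 = 0.732, and Φ(0.732) = 0.768

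The stepped-wedge variance formula, with the effect calibrated so that 130 gives 0.80, returns 0.770 at 120 whether 3, 4, 6 or 8 clusters are assumed. The figure of about 77 % therefore depends little on the layout, once it is accepted that 130 gives 80 %.

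**5. What each corrected figure delivers**

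- 163 × 0.80 = 130.4, so 130 are retained.
- 156 × 0.80 = 124.8, about 125, for which the same formula gives 0.784. The literal sum of the plan's own words is therefore still slightly short of 130 if a full 20 % leave.

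**The case against.** The arithmetic itself is hard to contest. The case on the other side is that little hangs on it, and several parts of that case stand.

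- **Leavers are not lost entirely.** Under Statistical analysis, the planned multilevel model handles repeated measurements within a participant, and pain is asked about every four weeks. Someone who leaves still contributes earlier responses, so counting only 120 overstates the loss of information. This stands, and makes 77 % an approximate lower figure.
- **150 is a minimum.** All employees of the nursing homes are eligible, and reminders and telephone calls are planned to limit missing answers. Enrolling more people would close the gap. This stands, but does not make the stated floor correct.
- **The error is small.** It is 6 people on the plan's wording, 13 on the stricter reading, and about 3 points of power. This stands, and bears on severity.

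Two stronger readings are tempting but not supported.

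- A reader might infer that the 20 % covers turnover alone and leaves nothing for survey drop-out. The sentence ("in employee turnover and risk of drop-out from questionnaire survey from other reasons, we added another 20" %) can equally be read as one allowance for both. The period over which turnover is counted is not given, while effectiveness is analysed after six months. A further separate loss would be the reader's own assumption.
- A reader might infer that the minimum is defective because it is set in people rather than in nursing homes, or that 130 implies a particular number of homes. The stated inputs are compatible with several layouts: ten homes in five steps give about 0.84 at 130 people, and two homes with several measurement periods per step give about 0.80. A condensed article may leave such detail to the full protocol.

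**Conclusion.** Wrong as written. The minimum of 150 does not follow from 130 and 20 %; the results are 156 or 163, depending on what the 20 % means. As stated, 150 covers a loss of 13.3 %, not 20 %. With a 20 % loss, 120 people remain and power is about 77 % instead of 80 %. That figure rests on three assumptions: that 130 analysable people give 80 %, that α is two-sided, and that those who leave contribute nothing. The last is pessimistic under the planned model.

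It would go too far to conclude that the trial fails to reach 80 % power outright. Absolute power depends on the numbers of homes, steps and measurements, which the article does not state with the calculation. Under one assumed layout (six homes, one crossing per step, one measurement per person per period, a raw difference of 0.5), 120 people would give 0.855. The supported conclusion is the conditional one above. Severity is modest: no analysis or estimand changes, but the sample size the trial relies on should agree with its own derivation.

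**What to change.** Correct the final sentence of Sample size calculation in one of these ways, according to what was intended:

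- 20 % was simply to be added: state 156.
- 130 were to remain after a 20 % loss: state 163.
- 150 was the intended floor: restate the allowance as about 13 % loss (about 15 % added).
- 150 and a 20 % loss were both intended: restate the retained number as 120, with power of about 77 % on the premise that 130 gives 80 %.

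It would help to say explicitly whether the percentage is an addition to the base or an expected loss from those enrolled. Each option costs one sentence. The last two need no extra recruitment; the first two raise the stated minimum by 6 and 13 people respectively.
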